### Number of consultations per clinic and health post:

In the 22 study clinic, there are 207 health posts (414 community health workers). The sample size will be limited by the number of consultations where an RDT will be deployed. The table shows the monthly activities report for the Health Posts in the study clinics for 3 months, from July-Sept 2010.

| **Province/clinic** | **Number of Health Posts** | **Number of treatments given for:** | | | |
| --- | --- | --- | --- | --- | --- |
|  |  | **Malaria** | **URTI** | **Diarrhoea** | **Total** |
| **Kunduz** | **65** | **47** | **2693** | **3161** | **5901** |
| Ajighan | 6 | 3 | 267 | 345 | 615 |
| AngorBagh | 7 | 3 | 568 | 823 | 1394 |
| ArbabRamazani | 2 | 2 | 54 | 73 | 129 |
| BolaQachi | 5 | 10 | 246 | 268 | 524 |
| CharSari | 6 | 2 | 245 | 205 | 452 |
| Khan Abad | 20 | 0 | 560 | 584 | 1144 |
| KhwajaGhaltan | 8 | 6 | 264 | 387 | 657 |
| Madrasa | 3 | 17 | 131 | 103 | 251 |
| Nick Pay | 3 | 0 | 36 | 49 | 85 |
| SandoqSai | 5 | 4 | 322 | 324 | 650 |
|  |  |  |  |  |  |
| **Nangarhar** | **142** | **2471** | **3736** | **3611** | **9818** |
| Baro | 8 | 63 | 158 | 230 | 451 |
| Batikot | 21 | 450 | 541 | 468 | 1459 |
| Behsood | 16 | 216 | 354 | 297 | 867 |
| Chardhi | 6 | 45 | 112 | 93 | 250 |
| GardiGhos | 6 | 310 | 342 | 281 | 933 |
| Khewa | 12 | 158 | 487 | 670 | 1315 |
| LandaBuch | 10 | 174 | 258 | 247 | 679 |
| MamandDara | 11 | 382 | 319 | 313 | 1014 |
| NajmulQura | 6 | 189 | 291 | 329 | 809 |
| Rodat | 13 | 52 | 50 | 37 | 139 |
| SangarSarai | 18 | 212 | 271 | 338 | 821 |
| Shegay | 15 | 220 | 553 | 308 | 1081 |
| **Grand Total** | **207** | **2518** | **6429** | **6772** | **15719** |

### Sample size:

An initial sample size of 1500 was selected for phase I to assess the secondary outcome of number of malaria positive patients correctly treated. Because Pf malaria is rare, the study is not powered for assessing the proportion of Pf cases correctly treated, although this will be examined as an exploratory analysis. For Phase II an initial sample size of 4000 individuals would assess the same secondary outcome, adjusted for cluster sampling. The confidence level (alpha) is 0.05 and the power (beta) is 0.8.

The sample size for both phases is adjusted for both intra-cluster variation (intra-cluster correlation coefficient of 0.5). To give a harmonic mean (see section 2.5.3) of 68 patients per cluster for phase I and 182 for phase II sample sizes of 2542 and 6792 are required in phase I and phase II respectively. This step is discussed in more detail in section 2.5.3.

|  |  | **Phase I** | | **Phase II** | |
| --- | --- | --- | --- | --- | --- |
| **Clinic** | **Province** | **SS weighting by cluster size** | **SS Weighted by cluster size for harmonic mean of 68** | **SS weighting by cluster size** | **SS Weighted by cluster size for harmonic mean of 182** |
| Ajighan | KDZ | 73 | 124 | 194 | 330 |
| AngorBagh | KDZ | 163 | 276 | 435 | 739 |
| ArbabRamazani | KDZ | 15 | 25 | 41 | 70 |
| BolaQachi | KDZ | 66 | 112 | 175 | 297 |
| CharSari | KDZ | 52 | 88 | 138 | 234 |
| Khan Abad | KDZ | 147 | 249 | 392 | 666 |
| KhwajaGhaltan | KDZ | 66 | 112 | 176 | 299 |
| Madrasa | KDZ | 30 | 51 | 80 | 136 |
| Nick Pay | KDZ | 12 | 20 | 33 | 56 |
| SandoqSai | KDZ | 63 | 107 | 169 | 287 |
| Baro | NGR | 37 | 63 | 100 | 170 |
| Batikot | NGR | 121 | 205 | 322 | 547 |
| Behsood | NGR | 72 | 122 | 191 | 324 |
| Chardhi | NGR | 21 | 36 | 55 | 93 |
| GardiGhos | NGR | 77 | 130 | 206 | 350 |
| Khewa | NGR | 109 | 185 | 290 | 493 |
| LandaBuch | NGR | 56 | 95 | 150 | 255 |
| MamandDara | NGR | 84 | 142 | 224 | 380 |
| NajmulQura | NGR | 67 | 114 | 178 | 302 |
| Rodat | NGR | 12 | 20 | 31 | 53 |
| SangarSarai | NGR | 68 | 115 | 181 | 307 |
| Shegay | NGR | 89 | 151 | 238 | 404 |
| Sample Size | | 1500 | 2542 | 3999 | 6792 |
|  |  |  |  |  |  |
| Arithmetic Mean | | 68.1818182 | 115.5455 | 181.7727273 | 308.7273 |
| Harmonic Mean | | 40.1240439 | 67.61738 | 107.1515805 | 182.1944 |
| Ratio (arithmetic:harmonic) | | 1.69474 |  | 1.69853 |  |

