### Balance criteria:

The following variables that are expected to be important correlates of the primary outcome and on which we wish to achieve balance were based on a data collected in 2009 in the same study clusters and over the same study period i.e. July to December.

1. Harmonic mean. For a given number of clusters and overall sample size maximum statistical efficiency is obtained if an equal number of patients per cluster are selected. The total sample size of 1500 across 22 clusters would require an *arithmetic* mean of 68 patients per cluster. However, due to the huge variability in the proportion of patients seen with suspected diarrhoea, URTI and malaria (when CHWs are likely to use RDTs) per cluster this approach was not seen as appropriate for several reasons including time to reach sample size quota, and cluster representation. Hence the sample size was weighted according to the cluster proportion of patients seen with suspected diarrhoea, URTI and malaria to achieve a *harmonic* mean of 68 patients per cluster in each arm. Since the sample size calculation was done before randomisation the overall harmonic mean (for all clusters) was used but this does not guarantee a harmonic mean of 68 per arm and therefore this was included as a restriction factor in the randomisation.
2. Total sample size. The precision and power of a study are usually maximised when sample sizes are similar in the treatment arms. In CRTs this means that the number of clusters as well as the number of individuals should be similar across treatment arms. Therefore, due to the variability in sample size per cluster this was also added as a restriction factor.
3. Number of health posts. There is a substantial amount of variation in the number of health posts per cluster from 2 to 26. Clusters (clinics) with bigger catchment populations have more health posts and therefore by balancing on this factor and equal sample size per arm will be achieved.

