## Sample Size and Statistical Methods:

### Sample Size Assumptions:

Key parameters and assumptions used to calculate the sample size are listed below:

- Number of clusters (clinics): 22
- Number of Health Posts: 207
- Number of CHWs: 414
- Expected difference in primary outcome in Phase 1 (40%):
  - Arm 1 - Non-intervention: 10% correctly treated vs.*
  - Arm 2 – RDT: 50% correctly treated*
- Expected difference in major secondary outcome (in phase 1):
  - Proportion of Pf positive patients receiving ACT: 0.5% in arm 1 vs. 50% in arm 2.*
  - Proportion of malaria negative patients treated with antimalarial: 90% in arm 1 vs. 50% in arm 2*
  - Proportion of malaria negative patients treated with antibiotic: 5% in non-intervention arm, 15% in RDT arm.
- Expected difference in primary outcome in Phase 2 (20%):
  - Arm 2 – RDT: 50% correctly treated.
  - Arm 3 – RDT extended programme: 70% or greater are correctly treated.
- Expected differences in major secondary outcome (in phase 2):
  - Proportion of Pf positive patients receiving ACT: 50% in arm 2 vs. 85% in arm 3.
  - Proportion of malaria negative patients treated with anti-malarial: 50% in RDT arm, 25% in RDT extended programme arm.
  - Proportion of malaria negative patients treated with antibiotic: 15 % in RDT arm, 20% in RDT extended arm.
- Sub-group analysis assumes that 40% of patients are under 10yrs*.

* estimates are based on initial results from the current randomised trial, based on data from 22 clinics in Afghanistan. There are no estimates in this region for effectiveness at CHW level.

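### The sample size is set for correct treatment among malaria-positive patients, an outcome that is not listed and has no stated rates or positivity; the stated 80% power is not supported for it

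*Protocol*

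**What the plan says.** Section 2.8.3 ties both phases to one outcome. For Phase I: "An initial sample size of 1500 was selected for phase I to assess the secondary outcome of number of malaria positive patients correctly treated". For Phase II: "For Phase II an initial sample size of 4000 individuals would assess the same secondary outcome, adjusted for cluster sampling". It adds "The confidence level (alpha) is 0.05 and the power (beta) is 0.8" and an "intra-cluster correlation coefficient of 0.5"; 2.8.1 gives "Number of clusters (clinics): 22".

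The targets per cluster are harmonic means of 68 (Phase I) and 182 (Phase II) enrolled patients, which raises the totals to 2,542 and 6,792. On how they are spread over clinics, 2.5.3 says "the sample size was weighted according to the cluster proportion of patients seen with suspected diarrhoea, URTI and malaria".

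The table in 2.8.2 (July to September 2010) gives health posts, malaria, URTI, diarrhoea and total treatments. Its Kunduz row reads "Kunduz | 65 | 47 | 2693 | 3161 | 5901". A typical row of the quota table in 2.8.3 is "AngorBagh | KDZ | 163 | 276 | 435 | 739": 276 patients in Phase I from a clinic with 3 malaria treatments in the quarter.

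The primary outcome (2.6.1) pools PCR-positive and PCR-negative patients. The closest secondary outcomes in 2.6.2 are ACT treatment of Pf cases, for which 2.8.3 says the study is not powered, and parts of the per-policy composite. Section 2.8.1 gives rates for the primary outcome, for Pf cases and for malaria negatives, but none for malaria positives as a group.

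**The concern.** A sample size needs a defined outcome, assumed rates and the number of patients who will enter the outcome. Here the outcome is not in the outcome list, the rates are absent, and no step converts enrolled patients into malaria positives. The protocol therefore fixes 1,500 and 4,000 on something a reader cannot check.

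The spread of the quotas adds to this. Nearly half the patients are to come from a province with very few malaria treatments, so positives will be scarce in ten of the 22 clusters. At stake is whether a null or imprecise result on treatment of malaria positives would be read as coming from a trial with 80% power for that question.

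**Working it through.** **1. The plan's own figures.** The column sums and means in 2.8.3 reproduce: 1,500, 2,542, 3,999 and 6,792, with harmonic means 40.12, 67.62, 107.15 and 182.19. The 68 is 1,500/22. The 1,500 itself cannot be derived, because no rates are given for its outcome. With the primary-outcome rates (10% vs 50%) as a stand-in, two-sided alpha 0.05 and 80% power:
- n per arm = [1.96·√(2·0.3·0.7) + 0.8416·√(0.09+0.25)]²/0.4² = 19.4, so 20
- design effect = 1 + 67·0.5 = 34.5
- total = 2·20·34.5 = 1,380, not 1,500

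**2. Where the quotas lie.**
- Kunduz share of quotas: 1,164/2,542 = 45.8% (687/1,500 = 45.8% before inflation).
- Kunduz share of malaria treatments: 47/2,518 = 1.9%.
- Kunduz share of the 2.8.2 totals, the stated weights: 5,901/15,719 = 37.5%.
- Kunduz share of URTI plus diarrhoea alone: 5,854/13,201 = 44.3%.

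Neither weighting gives 45.8%. The ratio of uninflated quota to 2.8.2 total is about 0.10 to 0.14 in Kunduz clinics and 0.08 to 0.09 in Nangarhar clinics. Section 2.5.3 describes its balance data as July to December 2009, so the quotas may rest on other data; the source is not stated.

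**3. Expected positives (proxy).** Phase I quota × the clinic's malaria share in 2.8.2, for example AngorBagh 276 × 3/1,394 = 0.6.
- Kunduz: Ajighan 0.6, AngorBagh 0.6, ArbabRamazani 0.4, BolaQachi 2.1, CharSari 0.4, Khan Abad 0, KhwajaGhaltan 1.0, Madrasa 3.5, Nick Pay 0, SandoqSai 0.7; sum 9.2.
- Nangarhar: 6.5 to 63.2 per clinic; sum 346.7; harmonic mean 17.6.
- Total 356 of 2,542 (14%).

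**4. Information per clinic.** A clinic with k positives contributes k/(1+(k−1)·ICC). At ICC 0.5 this is 2k/(k+1): 1.0 for one positive, 1.89 for 17.6, never more than 2. I averaged this over a Poisson count around each expected number and summed over the allocated arms: 13.8 (no RDT) and 14.4 (RDT). Kunduz supplies 5.6 of 28.2, about 20%.

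**5. Phase I power, 10% vs 50% assumed.** Variance = 0.09/I₀ + 0.25/I₁, with I₀ and I₁ the summed information in the no-RDT and RDT arms; noncentral t, 20 df unless noted.

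| Scenario | Variance | 0.4/SE | Power |
| --- | --- | --- | --- |
| All clinics, ICC 0.5 | 0.09/13.82 + 0.25/14.39 = 0.0239 | 2.59 | 69% |
| Half of treatments true positives | 0.09/11.88 + 0.25/12.89 = 0.0270 | 2.44 | 64% |
| A quarter true positives | 0.09/9.85 + 0.25/11.18 = 0.0315 | 2.25 | 57% |
| Nangarhar alone (10 df) | 0.34·(0.5+0.5/17.6)/6 = 0.0299 | 2.31 | 55% |
| All clinics, ICC 0.3 | 0.09/20.06 + 0.25/21.65 = 0.0160 | 3.16 | 85% |
| Same 356 spread evenly, ICC 0.5 | 0.34·(0.5+0.5/16.2)/11 = 0.0164 | 3.12 | 84% |
| Pooled primary outcome, 68 per cluster | 0.34·(0.5+0.5/68)/11 = 0.0157 | 3.19 | 86% |

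Counting positives instead of all patients costs little by itself at this ICC (86% to 84%). The uneven spread of positives accounts for the fall to 69%.

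**The case against.** Several points on the other side are sound and limit the finding.

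- **Kunduz is not empty of information.** A reader might infer that the outcome rests on 12 clinics rather than 22, with 55% power. At ICC 0.5 even a clinic with one positive carries about half the information of a large one, and eight of the ten Kunduz clinics have a non-zero expectation. The 55% is a lower reference value, not the estimate.
- **Malaria treatments are not PCR positives.** They are CHW labels, and 2.8.1 itself expects 90% of negatives in arm 1 to receive an antimalarial. The 356 is a proxy, which is why a range is shown.
- **Malaria is among the stated weights.** A reader might blame URTI and diarrhoea weighting for the 46%. The 2.8.2 totals give 37.5%, so what stands is an unexplained quota source. The gap from 1.9% remains at either figure.
- **The entry rule is wider than antimalarial use.** A reader might infer that Kunduz CHWs must miss quota or enrol ineligible patients. Section 2.5.7 also admits patients for whom a test would be requested, and 2.5.3 justifies the weights by likely RDT use. Recruitment is a feasibility risk, not a contradiction.
- **The primary outcome counts every patient**, so Kunduz negatives inform it fully.

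Reweighting quotas by malaria treatments is no remedy. Khan Abad and Nick Pay would get zero. The allocated arms, with 901 and 1,617 treatments, would have quotas of 2,542·901/2,518 = 910 and 2,542·1,617/2,518 = 1,632, against the permitted difference of 50. A symptom-based entry rule would change the study population.

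None of this supplies the missing outcome, rates or positivity.

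**Conclusion.** The point holds in this form. The protocol states 80% power for an outcome it neither lists nor parameterises, and expresses its cluster sizes in patients who mostly do not enter that outcome. A later analysis plan cannot cure this, because the protocol itself fixes the numbers.

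On the protocol's ICC of 0.5, Phase I power for malaria positives is about 69%, and 57% to 64% if many treated patients are not true positives. This rests on three assumptions: 10% versus 50% among positives (borrowed from the primary outcome), malaria treatments as a guide to where positives arise, and a two-sided test. The shortfall depends on the ICC: at 0.3 the same counts give about 85%. More positives in Kunduz than the proxy suggests would also raise the power. So the stated 80% is unsupported for this outcome; it is not shown to be unattainable.

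A reader might also infer that the whole trial is underpowered in Phase I. The documents do not support that: the pooled primary outcome has about 86% at the stated 10% versus 50%.

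**What to change.** Choose one of two texts for 2.8.3:

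1. List correct treatment among PCR-positive patients in 2.6.2. Give its assumed rates in each arm and the assumed PCR positivity by province in 2.8.1, and restate the power for both phases on expected positives per cluster, with a range for the ICC.
2. State that the sample size rests on the pooled primary outcome, give the power for that, and describe the malaria-positive comparison as secondary without a power claim.

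Under option 2, Phase II needs its own figure, because the 86% is for Phase I only. With 50% versus 70%, 182 per cluster and ICC 0.5, the variance is 0.46·(0.5+0.5/182)/11 = 0.0210, the ratio 0.2/0.145 = 1.38, and power about 26%. The ICC would have to be justified there too.

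In either case, state the data source and period behind the quota table, and why it differs from the 2.8.2 totals.

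Leave the quotas, totals, entry rule and completed randomisation as they are. The cost is protocol text and a short recalculation, with no extra patients. The downside is a lower stated power for the malaria-positive outcome.

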### Trial Profile:

**Figure: Trial schematic for Phase 1.**

If the criteria for running phase 2 of the trial are met the 22 clinics will be re-randomised so that 50% of those clinics in arm 1 are randomised to arm 3 and 50% to arm 2, and 50% of those in arm 2 will be randomised to arm 3 with 50% remaining in arm 2 (figure 2).

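### Phase II size, clinic quotas and power of 0.8 are set on an unsourced ICC of 0.5 and an untested Arm 2 rate, with no step to update them from Phase I

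*Protocol*

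**What the plan says.** Protocol section 2.8.3 bases the Phase I size on a secondary outcome: 1500 patients were chosen "to assess the secondary outcome of number of malaria positive patients correctly treated". For the second phase it says: "For Phase II an initial sample size of 4000 individuals would assess the same secondary outcome, adjusted for cluster sampling". Both phases use an "intra-cluster correlation coefficient of 0.5", with no source. The error rates are given as: "The confidence level (alpha) is 0.05 and the power (beta) is 0.8".

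The totals are then enlarged so that the harmonic mean per clinic is 68 in Phase I and "182 for phase II sample sizes of 2542 and 6792 are required in phase I and phase II respectively". The table below that text gives a Phase II quota for every clinic.

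Section 2.8.1 lists 50% correctly treated in Arm 2 and 70% or more in Arm 3 for Phase II. The Phase II rates carry no asterisk. The Arm 2 value repeats the asterisked Phase I figure, which comes from the earlier clinic-level trial. The note to that list adds: "There are no estimates in this region for effectiveness at CHW level".

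Phase II is conditional: "If the criteria for running phase 2 of the trial are met the 22 clinics will be re-randomised" (section 2.5.6). Section 2.5.1 starts it after Phase I, keeps the same outcomes and lets Phase I results shape the Arm 3 package. Section 3.4 lists an interim analysis. None of these places mentions revising the Phase II size, quotas or power.

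**The concern.** The trial is run in sequence, and its first phase produces most of the planning values that its second phase lacks. With 22 clinics fixed, the ICC sets a ceiling on power that no number of patients can lift. Positivity decides how many of the enrolled patients count towards the outcome used for sizing. The Arm 2 rate decides how much room is left for Arm 3. Phase I observes all of these in the same clinics, and its results have to be read anyway to decide whether Phase II runs.

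Without an update step, Phase II could start with a power statement that Phase I data already contradict. It could also enrol to quotas far from what is useful or achievable. The quotas are weighted on earlier malaria, URTI and diarrhoea counts. The ten Kunduz quotas sum to 3114 of 6792, yet Kunduz health posts reported 47 malaria treatments in three months (section 2.8.2). Only Phase I will show how many patients there meet the inclusion criterion that malaria is considered.

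**Working it through.** **1. The plan's own figures.** The unweighted Phase II quotas sum to 3999. Multiplying by the table's "Ratio (arithmetic:harmonic" value gives 3999 × 1.69853 = 6792, and the harmonic mean of the weighted quotas is 182.19. The step from 4000 to 6792 therefore reproduces.

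The 4000 does not reproduce from the stated inputs. Section 2.8.3 gives no rates for malaria-positive patients, so only the listed contrasts can be tried. For 50% v 70%, two-sided 5% (sidedness assumed) and 80% power, 93 patients per arm are needed before clustering. The design effect is 1 + (182 − 1) × 0.5 = 91.5, so the total is 2 × 93 × 91.5 = about 17,019. Working back, 4000 / 186 = 21.5, which corresponds to an ICC of (21.5 − 1) / 181 = 0.113.

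None of the four Phase II contrasts in section 2.8.1 reaches 0.8 at ICC 0.5 by this formula, even if all 182 patients per clinic counted: 27% (50 v 70), 71% (50 v 85), 40% (50 v 25) and 6% (15 v 20).

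**2. All-patient primary contrast.** Cluster-level t-test, 11 clinics per arm, 20 df, two-sided 5%:

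Variance of the difference = [p1(1−p1) + p2(1−p2)] / 11 × [ICC + (1−ICC)/HM], where HM is the harmonic mean per clinic.

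At ICC 0.5 and HM 182.2: (0.25 + 0.21)/11 × (0.5 + 0.5/182.2) = 0.0418 × 0.5027 = 0.0210. The standard error is 0.145, the non-centrality 0.20/0.145 = 1.38, and the power 26%.

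| ICC | Power, HM 182 | Power, HM 68 |
|---|---|---|
| 0.05 | 98% | 96% |
| 0.10 | 82% | 79% |
| 0.20 | 54% | 53% |
| 0.30 | 39% | 39% |
| 0.50 | 26% | 26% |

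For this contrast the extra 6792 − 2542 = 4250 patients add at most about 3 points.

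**3. Malaria-positive outcome.** The protocol states neither positivity nor rates among positives. Assume 50% v 70% among positives and the same positivity in every clinic, so that HM becomes 182.2 or 67.6 times positivity. Power at HM 182 v HM 68:

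| Positivity | ICC 0.05 | ICC 0.10 | ICC 0.20 | ICC 0.50 |
|---|---|---|---|---|
| 5% | 66% v 37% | 55% v 34% | 41% v 29% | 24% v 21% |
| 10% | 83% v 57% | 67% v 49% | 47% v 38% | 25% v 23% |
| 20% | 92% v 77% | 75% v 63% | 51% v 45% | 26% v 25% |

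The gain is about 12 to 29 points at ICC 0.05 to 0.10, and about 1 to 3 points at ICC 0.5.

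**4. How well Phase I can inform the ICC.** The ANOVA approximation is SE = sqrt{2(1−r)²(1+(m−1)r)² / [m(m−1)(k−1)]}, with r the ICC, m = 68 patients per clinic and k clinics. For k = 22 it gives 0.032, 0.053 and 0.079 at r = 0.1, 0.2 and 0.5. For the 11 RDT clinics alone it gives 0.046, 0.076 and 0.114. The unequal Phase I quotas (20 to 276) make the true precision somewhat worse.

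**The case against.** The strongest reply is that Phase II is sized on malaria-positive patients, so power for the all-patient contrast is the wrong yardstick. A reader might infer from the first table that the extra patients bring no return and that the ICC alone decides. That holds only for the all-patient contrast. For malaria-positive patients the larger clusters can be worth a great deal at low ICC, as the second table shows.

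A reader might also infer that Phase I will replace every Phase II input. It will not. Phase I has no Arm 3, so the 70% and the 20-point effect remain design choices. Half of the Phase II Arm 2 clinics will be former Arm 1 clinics, so the Phase I Arm 2 rate is informative but not identical. Nor are the Phase II rates documented as clinic-based: they carry no asterisk, and for Arm 2 the link is an inference from the repeated 50%.

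It would be too strong to say that 6792 is irrevocably committed. The text calls the 4000 initial, makes Phase II conditional and promises a fresh allocation, and nothing forbids an update. An analysis plan not shown here might also contain one. This softens the point but does not remove it: the protocol itself says the 6792 are required, sets quotas clinic by clinic, and states a power that its own ICC does not support for any contrast it lists.

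Finally, an ICC from 22 clinics, or from 11, is imprecise. That stands, and is a reason to report a range rather than a single power.

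**Conclusion.** The point holds as a gap in the design that should be closed. The Phase II size, quotas and power rest on an unsourced ICC of 0.5 and an Arm 2 rate not yet observed among CHWs, and no visible step updates them from the phase that will measure both. At the stated ICC, the 50% v 70% contrast has about 26% power against a stated 0.8. It has 54% at ICC 0.20 and 82% at 0.10. Whether the 4250 additional patients are valuable or nearly useless for the malaria-positive outcome depends on the ICC and positivity, both of which Phase I will measure.

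These figures assume a two-sided 5% test, 11 clinics per arm and a cluster-level t-test. Those for malaria-positive patients also assume 50% v 70% and 5% to 20% positivity, none of which the protocol states for that group.

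**What to change.** Mark the Phase II column in section 2.8.3, and its power, as provisional, and show how the 4000 was obtained. Add one pre-specified step before the Phase II allocation:

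- Re-estimate from Phase I the within-arm, within-province ICC (especially in RDT clinics), the Arm 2 proportion correctly treated (all patients and PCR-positive), PCR positivity and eligible patients per clinic.
- Recompute the quotas, total and power for both the primary and the malaria-positive outcome, keeping the Arm 3 target effect as a design choice.
- Give power as a range over the uncertainty in the ICC (SE about 0.03 to 0.08 with 22 clinics, 0.05 to 0.11 with 11), and restate it if 22 clinics cannot deliver 0.8.

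The cost is a short calculation on data already needed for the decision to run Phase II, plus a revised quota table. There is no alpha cost, because Phase II is a separate comparison in newly enrolled patients.

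### At the printed ICC of 0.5 with 11 clinics per arm, none of the listed Phase II contrasts reaches the stated power of 0.8; the primary contrast has about 26% however many patients each clinic enrols

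*Protocol*

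**What the plan says.** Section 2.8.3 (Sample size) gives one statement of error rates for both phases: "The confidence level (alpha) is 0.05 and the power (beta) is 0.8". It adjusts both phases for an "intra-cluster correlation coefficient of 0.5". Phase II starts at 4000 patients and is raised to 6792 so that the harmonic mean clinic size is 182. The section ties the 1500 (Phase I) and the 4000 (Phase II) to a secondary outcome, correct treatment among malaria-positive patients. It adds that the study is not powered for correct treatment of Pf cases.

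Section 2.8.1 (Sample Size Assumptions) lists "Number of clusters (clinics): 22". For the Phase II primary outcome it gives an expected 20-point difference: "Arm 2 – RDT: 50% correctly treated" against an extended-programme arm in which "70% or greater are correctly treated". The other Phase II contrasts are 50% v 85% (Pf patients given ACT), 50% v 25% (malaria-negative patients given an antimalarial) and 15% v 20% (malaria-negative patients given an antibiotic). No rates are given for malaria-positive patients as a whole.

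Section 2.5.6 (Trial Profile) re-randomises the same clinics for Phase II: "50% of those clinics in arm 1 are randomised to arm 3 and 50% to arm 2", with the Phase I RDT clinics split in the same way.

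**The concern.** An ICC of 0.5 is very high. At that value nearly all the variance of a clinic's observed proportion lies between clinics, so power depends on the number of clinics and hardly at all on patients per clinic. The protocol fixes the clinics at 22 and lets only the patient numbers grow from Phase I to Phase II, while the expected primary difference halves from 40 to 20 points.

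Phase II is the test of whether the extended programme improves on the standard rollout. If the printed ICC is right, a true rise from 50% to 70% would be missed about three times in four. A reader who saw only the 0.8 could take such a result as evidence that the extra support does not help.

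**Working it through.** **Inputs.** Alpha 0.05 and ICC 0.5 (2.8.3); 22 clinics (2.8.1); harmonic mean clinic size *m* = 182 in Phase II and 68 in Phase I (2.8.3); expected rates (2.8.1). Two assumptions are added. The test is two-sided, since sidedness is not stated. There are 11 clinics per arm in Phase II: each Phase I arm has 11 clinics and cannot be halved exactly, but 11 v 11 overall is possible.

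**The plan's own figures.** The table in 2.8.3 reproduces: harmonic means 67.6 and 182.2, totals 2542 and 6792. The 0.8 cannot be reproduced for the outcome it is attached to, because that outcome has no expected rates. It can be checked only against the contrasts that are listed.

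**Ceiling on information.** Effective n per arm = 11*m* / (1 + (*m* − 1) × ICC).
- At *m* = 182: 2002 / 91.5 = 21.9.
- With unlimited *m*: 11 / 0.5 = 22.

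**Power.** Var(difference) = [p1(1 − p1) + p2(1 − p2)] × (ICC + (1 − ICC)/*m*) / 11, with a noncentral t on 20 df. For the Phase II primary: (0.25 + 0.21) × 0.50275 / 11 = 0.0210; SE 0.145; 0.20 / 0.145 = 1.38; power 26%.

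| Phase II contrast | Difference / SE | Power |
|---|---|---|
| 50% v 70% (primary) | 0.20 / 0.145 = 1.38 | 26% |
| 50% v 25% | 0.25 / 0.141 = 1.77 | 39% |
| 15% v 20% | 0.05 / 0.115 = 0.44 | 7% |
| 50% v 85% (Pf) | 0.35 / 0.131 = 2.66 | at most 72% |

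The Pf figure is a ceiling because it treats all 182 patients per clinic as Pf cases.

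**Effect of clinic size on the primary.** 25.6% at 40 patients per clinic, 25.8% at 68, 26.0% at 182 and 26.1% with no limit.

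**Effect of method.** A pooled z gives 26.7%, an unpooled z 28.1%, and the actual unequal clinic sizes 26.7%. One-sided testing gives 38% to 40%.

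**What would give 80% for 50% v 70%.** About 47 clinics per arm (46 gives 79.7%, 47 gives 80.5%), or an ICC of at most about 0.105 with 11 per arm. With 11 per arm at ICC 0.5, the smallest detectable difference from 50% is about 38 points (50% v 88% gives 81%).

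**Phase I check.** 10% v 50% at *m* = 68: (0.09 + 0.25) × 0.50735 / 11 = 0.0157; SE 0.125; 0.40 / 0.125 = 3.19; power 86%.

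**Sensitivity of the Phase II primary.**
- ICC 0.2 gives 54%, 0.1 gives 82% and 0.05 gives 98%.
- At ICC 0.5, an arm 3 rate of 80% gives 55% power and 90% gives 86%.

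**0.5 read as a between-cluster coefficient of variation.** Clinics per arm = 1 + 7.85 × [p1(1 − p1)/*m* + p2(1 − p2)/*m* + 0.25(p1² + p2²)] / (p1 − p2)². For 50% v 25% at *m* = 182 the bracket is 0.0024 + 0.0781 = 0.0805, and 1 + 7.85 × 0.0805 / 0.0625 = 11.1, almost exactly this design (79.6% power with 11). The primary would still have only 31% (50% v 70% correct) or 57% (50% v 30% incorrect).

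**The case against.** **The 0.8 is not stated for the primary outcome.** This stands. A reader might infer that the protocol claims 80% for 50% v 70%, but section 2.8.3 ties the sample size to the malaria-positive outcome. That does not rescue the figure. The outcome is measured in the same 22 clinics, meets the same ceiling of 22, and has no rates from which 80% could be derived. Borrowing 50% v 70% and assuming 5% to 20% positivity (no figure is given) yields about 24% to 26% at ICC 0.5.

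**The 0.5 may be a misprint or a mislabelled coefficient of variation.** Either is possible and neither is shown: Phase I fits a literal ICC of 0.5, while 50% v 25% fits the coefficient-of-variation reading. A reader might go further and say that the stated power is wrong even if 0.05 was meant, because the primary would then have 98%. The document does not support that. For the malaria-positive outcome, with the same borrowed rates, ICC 0.05 gives 66%, 83% or 92% at 5%, 10% or 20% positivity, so 80% lies within the range.

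**Patient numbers still matter.** A reader might infer that the inflation to 6792 buys nothing and can be dropped. That holds only for outcomes measured in all patients. At 5% to 10% positivity (assumed), the inflation reduces the variance for malaria-positive outcomes by about 6% to 4% in Phase II even at ICC 0.5. The under-10 analysis and RDT sensitivity also depend on patient counts.

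**Other limits.** The protocol disclaims power for Pf cases, so the 72% is not a broken promise. A one-sided test would bring 50% v 85% just above 80%, but only if every patient were a Pf case. Randomisation is stratified by province; if part of the 0.5 lies between provinces, a stratified analysis would recover some power, by an amount that cannot be computed from the document. Phase II is also conditional on criteria being met.

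**Conclusion.** The concern holds in this form: section 2.8.3 states a power of 0.8 that the Phase II design does not deliver, under its own ICC and number of clinics, for any contrast in section 2.8.1, and the outcome used for sizing has no rates that would allow a check. For the primary contrast the power is about 26%, and more patients per clinic cannot raise it. The Phase I primary is not affected.

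This rests on the ICC as printed, a two-sided test, 11 clinics per arm, no credit for stratification, and 70% as the design value for arm 3. The ceiling is arithmetic. The 26% is conditional: an ICC near 0.1 would bring the primary contrast to about 80%, and an arm 3 rate near 90% would do so at ICC 0.5. The document does not establish that 0.5 is an error, that 80% was promised for the primary outcome, or that the 6792 target is wasteful.

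**What to change.** 1. Confirm or correct the 0.5, and say whether it is an ICC or a between-cluster coefficient of variation, and for which outcome.
2. Re-estimate it from Phase I CHW data before Phase II starts (February 2012 by section 2.5.1). Phase I is the natural source, because section 2.8.1 notes that no CHW-level estimates exist for the region. With 22 clinics the estimate will be imprecise, so give a range.
3. Replace the single 0.8 with the Phase II power and detectable difference for the primary contrast. Do the same for the malaria-positive outcome, with its expected rates and assumed positivity stated. Say that the number of clinics is the limit. Keep the patient target under review for the malaria-positive and subgroup outcomes rather than cutting it on the strength of the primary.
4. Adjust the Phase II comparison for each clinic's Phase I proportion, taken within Phase I arm. If the two proportions correlate at *r*, the variance is multiplied by 1 − *r*². At *r* = 0.5 the ratio becomes 1.38 / √0.75 = 1.59 (about 33% power), and at *r* = 0.7 it becomes 1.38 / √0.51 = 1.93 (about 45%). The 0.5 to 0.7 is an assumption; Phase I alone cannot supply it.

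The cost is protocol text, one ICC estimate that needs the Phase I PCR results in time, and a less favourable stated power if the ICC stays near 0.5. No extra patients are needed.
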